**Belo Horizonte**

**Universidade Federal de Minas Gerais**

**School of Physical Education, Physiotherapy, and Occupational Therapy**

**2021**

## **ABSTRACT:**

**Background:** Individuals with PD commonly have a significant reduction in respiratory muscle strength and inspiratory muscle endurance, and it can intensify with the disease progression. Respiratory muscle training has been shown to increase respiratory muscle strength in individuals with Parkinson's disease (PD). However, the effect size on other functional outcomes has not been determined and/or investigated. In addition, studies investigating the effects of high-intensity respiratory muscle training (inspiratory and expiratory) in this population were not found.

**Objectives:** To investigate the efficacy of high-intensity respiratory muscle training (combined inspiratory and expiratory muscle training) in improving inspiratory and expiratory muscle strength, inspiratory muscle endurance, peak cough flow, dyspnea, fatigue, exercise capacity, and quality of life in this population.

**Design:** A randomized controlled trial with blinded evaluation will assign eligible participants to either high-intensity respiratory muscle training (experimental group) or sham training (control group). Individuals will perform a home-based intervention, not directly supervised, consisting of two daily 20-min sessions (morning and afternoon), seven times a week, during eight weeks. Study Outcomes: Primary outcomes are inspiratory and expiratory muscle strength. Secondary outcomes are respiratory muscle endurance, peak cough flow, dyspnea, fatigue, exercise capacity, and quality of life. The outcomes will be measured at baseline, post-intervention (after the 8-week intervention), and one month after the cessation of the intervention (12-week follow-up), by trained evaluators.

**Conclusion:** The results of this trial will provide valuable new information on the effects of high-intensity respiratory muscle training in improving muscle strength and other

functional outcomes in individuals with PD.

## **1.0. Introduction and Literature Review**

### **1.1. Parkinson's Disease**

Neurological diseases are the leading cause of disability worldwide (GROUP, 2015). Among the diseases analyzed by the Global Burden of diseases, injuries, and risk factors study, Parkinson's disease (PD) was the one with the highest growth in prevalence, disabilities, and deaths (GROUP, 2015). From 1990 to 2016, there was a 2.4-fold increase in the number of people with PD (DORSEY et al., 2007). PD is the second most prevalent neurodegenerative disease globally. It is estimated that approximately 6.1 million people have PD worldwide (DORSEY et al., 2016). However, these numbers may be underestimated, since there are few official data on the incidence and prevalence of PD in many countries, especially underdeveloped and developing ones (DORSEY et al., 2016), such as Brazil.

A study carried out in a Brazilian city showed a prevalence of 3.3% of PD among older adults (BARBOSA et al. 2006). According to statistics, there are approximately 30 million older adults in Brazil (CONTINUA, 2020). If this prevalence is extrapolated to the older population in Brazil, it is projected that approximately one million Brazilians have PD. Furthermore, estimates indicate that the incidence of PD will approximately double by 2030 (DORSEY et al., 2007).

PD is a degenerative and progressive disease of the central nervous system that causes motor and non-motor disabilities (KALIA et al., 2015). The neuropathology of PD is multifactorial and heterogeneous, but there are some pathological hallmarks (MCGREGOR et al., 2019). A neuropathological hallmark is the presence of intracellular inclusions resulting from the aggregation of the  $\alpha$ -synuclein protein, called Lewy bodies (KALIA et al., 2015). The most well-known site of Lewy body deposition and neurodegeneration is the midbrain, specifically the dopaminergic neurons of the

substantia nigra pars compacta (MCGREGOR et al., 2019). This leads to loss of dopamine in the nigrostriatal system (KALIA et al., 2015). Finally, other non-dopaminergic systems are also affected by disease progression, such as cholinergic, serotonergic, and noradrenergic projections (MCGREGOR et al., 2019; SCHAPIRA et al., 2017).

PD has four classic motor signs (bradykinesia, rigidity, postural instability, and resting tremor), called cardinal signs (KALIA et al., 2015; MORRIS et al., 2000; SCHEKMAN et al., 2001; SHULMAN et al., 2011). In addition, PD causes various non-motor disabilities as well, such as ventilatory and respiratory disorders, cognitive deficits, fatigue, autonomic dysfunction, sleep disturbances, and gastrointestinal disorders (KALIA et al., 2015).

The International Classification of Functioning, Disability, and Health (ICF) (ORGANIZAÇÃO MUNDIAL DE SAÚDE, 2003) provides an important framework for describing functionality, guiding therapeutic goal setting and intervention plans. In the study by Raggi et al. (2011), individuals with PD reported impairment in body structures and functions, activity limitations, and restrictions on social participation (RAGGI et al. 2011). In addition, environmental factors were qualified as barriers or facilitators, such as attitudes of family members and policies of social security services (RAGGI et al. 2011).

## **1.2. Respiratory Disorders in Parkinson's Disease**

Respiratory and ventilatory disorders are non-motor signs and symptoms commonly observed in individuals with PD. According to studies, individuals with PD commonly have respiratory muscle weakness (HAAS et al., 2004; GUEDES et al., 2012; PAL et al., 2007; SANTOS et al. 2019), reduced lung function, altered kinematics of the

rib cage, reduced laryngeal sensitivity, and compromised cough reflex (EBIHARA et al., 2003; FONTANA et al., 1998; PITTS et al., 2008). The prevalence of respiratory disorders in PD is still underestimated. In a literature review, it was reported that the prevalence of restrictive disorders in individuals with PD ranged from 28% to 94%, and obstructive disorders ranged from 6.7% to 67% (D'ARRIGO et al., 2020).

The pathophysiology of respiratory disorders in PD is still uncertain. Biomechanical characteristics of PD may be related to the respiratory disorders found in these individuals, such as postural changes and stiffness in the thoracic muscles, reduced thoracic mobility (CARDOSO et al., 2002), changes in the activation and coordination of the upper airway muscles (MONTEIRO et al., 2014). In addition, tremors (BROWN et al., 1997) and bradykinesia can compromise the respiratory function in individuals with PD (CARDOSO et al., 2002; GUEDES et al., 2012).

Neuropathological changes have also been associated with these respiratory disorders. As previously described, one of the neuropathological characteristics of PD is the depletion of dopaminergic neurons in the substantia nigra of the midbrain. This neuronal destruction also happens in the brain, as in the brainstem nuclei that control sleep and breathing. In addition, aggregation of the  $\alpha$ -synuclein protein occurs first in the medulla, and later in the respiratory centers (BRAAK H., 2003; DOCU AXELERAD et al., 2021).

It has been widely described in the scientific literature that individuals with PD have reduced respiratory muscle strength when compared to healthy individuals of the same sex and age. Guedes et al. (2012) found maximum inspiratory pressure (MIP) and maximum expiratory pressure (MEP) values significantly lower in individuals with PD (MIP (men)=  $65.0 \pm 17.9 \text{ cmH}_2\text{O}$ ; MIP (women)=  $55.6 \pm 18.8 \text{ cmH}_2\text{O}$ ; MEP (men)=  $81.9 \pm 14.7 \text{ cmH}_2\text{O}$ ; MEP women=  $64.4 \pm 21.9 \text{ cmH}_2\text{O}$ ) when compared to healthy

individuals of the same sex and age (MIP (men)=  $86.9 \pm 6.2 \text{ cmH}_2\text{O}$ ; MIP (women)=  $70.0 \pm 14.1 \text{ cmH}_2\text{O}$ ; MEP (men)=  $120.0 \pm 29.4 \text{ cmH}_2\text{O}$ ; MEP (women)=  $105.6 \pm 19.4 \text{ cmH}_2\text{O}$ ) (GUEDES et al. 2012).

Studies have already shown that the reduction in respiratory muscle strength is present in the early stages of PD (BAILLE et al., 2019) and that it intensifies with the progression of the disease (SANTOS et al. 2019). Although respiratory disorders are frequent and potentially serious, it may not be observed early due to the reduced level of physical activity of individuals with PD (HAAS et al., 2004; HOVESTADT et al., 1989; SATHYAPRABHA et al., 2005). Due to the reduced level of physical activity, these individuals may not perform activities that require sufficient energy expenditure to manifest signs of respiratory dysfunction. (VAN NIMWEGEN et al., 2011). Therefore, interventions to improve respiratory muscle strength are commonly initiated in advanced stages.

As previously described, individuals with PD may have reduced muscle strength in both inspiratory and expiratory groups. Both muscle groups are essential for maintaining adequate respiratory function. In individuals with PD, it has already been observed that inspiratory muscle weakness predisposes to the onset of atelectasis and secretion retention, which is an important risk factor for infections (SAPIENZA et al., 2003). In expiratory muscle weakness, there is an increased risk of accumulation of secretions and the development of respiratory complications, such as pneumonia (BACKSTROM et al., 2018). Therefore, both inspiratory and expiratory muscle strength should be measured in individuals with PD and, when muscle weakness is observed, interventions to increase muscle strength of both muscle groups should be performed.

### **1.3. Respiratory Muscle Training**

Several therapeutic interventions have been used to increase respiratory muscle strength in these individuals (HAAS et al. 2004; KILLIAN et al., 1984; MCMAHON et al. 2020; SANTOS et al. 2011). A systematic review with meta-analysis assessed the effects of non-pharmacological interventions on the respiratory function of individuals with PD (MCMAHON et al. 2020). In this systematic review, studies that assessed the effects of several kinds of interventions were included, such as, such as aerobic exercise, yoga, cycling, peripheral muscle strengthening, and specific strengthening of the respiratory muscles (inspiratory and expiratory muscle training) (MCMAHON et al. 2020).

The results of this meta-analysis demonstrated that global exercises and respiratory muscle training had a statistically significant increase in respiratory muscle strength, peak expiratory flow, and respiratory muscle endurance (MCMAHON et al. 2020). In addition, respiratory muscle training significantly increased peak cough flow and dyspnea, but it was not possible to perform a meta-analysis for these outcomes due to data heterogeneity, (MCMAHON et al. 2020).

Respiratory muscle training has the potential to improve respiratory function (MCMAHON et al. 2020). Systematic reviews with meta-analysis have already demonstrated that respiratory muscle training is effective in increasing the respiratory function of individuals with different health conditions, such as individuals with chronic obstructive pulmonary disease (SHAFFER et al., 1995), heart failure (MCELFRESH et al., 2012), stroke (MENEZES et al., 2016) and in mechanical ventilation (ELKINS et al., 2015). In individuals with PD, a systematic review of randomized controlled trials (RCT) investigated the effects of respiratory muscle strengthening on respiratory function (RODRÍGUEZ et al. 2020). Only five studies from three different RCTs were included. Of these five studies, one investigated the effect of inspiratory muscle training on

inspiratory muscle strength, respiratory muscle endurance, reduction of dyspnea, and quality of life (INZELBERG et al. 2005). Two studies from a single RCT evaluated the effect of expiratory muscle strengthening on swallowing (TROCHE et al., 2010), expiratory muscle strength, and lung function (SAPIENZA et al., 2011). In addition, in two other studies from a single RCT, the effectiveness of respiratory muscle training at peak cough flow, inspiratory and expiratory muscle strength (REYES et al., 2018), and phonatory parameters (REYES et al., 2019). Finally, in two other studies from a single RCT, the effects of respiratory muscle training on peak cough flow, inspiratory and expiratory muscle strength (REYES et al., 2018), and phonatory parameters (REYES et al., 2019) were investigated.

In those previous studies, the training load ranged from 15% to 60% of MIP (INZELBERG et al. 2005) and ranged from 50% to 75% of MEP (REYES et al. 2018; REYES et al. 2019; SAPIENZA et al. 2011; TROCHE et al. 2010), duration ranged from four (SAPIENZA et al. 2011; TROCHE et al. 2010) to 12 weeks (INZELBERG et al. 2005) and frequency from five to six times a week (INZELBERG et al. 2005; REYES et al. 2018; REYES et al. 2019). It was not possible to evaluate the superiority of one protocol over the other due to heterogeneity in outcome measures. The systematic review demonstrated that respiratory muscle training is effective in improving respiratory muscle strength and endurance, lung function, swallowing, dyspnea, and phonatory parameters in individuals with PD (RODRÍGUEZ et al., 2020). However, a small number of studies were found (only three RCTs). In addition, it has been shown that existing studies have moderate methodological quality and heterogeneity in their outcome measures (RODRÍGUEZ et al., 2020). Therefore, the authors concluded that the evidence is limited for any recommendation for clinical practice, suggesting the execution of other RCTs (RODRÍGUEZ et al., 2020).

In these studies, an increase in MIP was found, ranging from -1.28cmH2O (INZELBERG et al., 2005) to -16cmH2O (REYES et al., 2018). In addition, increases in MEP from 15.5cmH2O (REYES et al., 2018) to 27.97cmH2O (SAPIENZA et al., 2011) were observed when expiratory muscle training was performed. In other studies that investigated the effect of high-intensity respiratory muscle training in other populations, an improvement in MIP of -43cmH2O and MEP of 51cmH2O was found, that is, approximately double (GOMES NETO et al., 2018; HILL et al., 2006; PARREIRAS DE MENEZES et al., 2019). In addition, the benefits of respiratory muscle training on other functional outcomes (perception of dyspnea, fatigue, and exercise capacity) seem to be obtained when a high training volume (load, duration, and frequency) is applied (GOMES NETO et al., 2018; HILL et al., 2006). Therefore, the effects of high-intensity respiratory muscle training of higher intensities (load, intensity, and volume) still need to be investigated in individuals with PD.

Studies investigating the effects of respiratory muscle training on fatigue, and exercise capacity in individuals with PD were not found. In individuals with other neurological diseases, respiratory muscle training has been shown to improve performance in activities of daily living (CHEN et al., 2016), exercise capacity (SUTBEYAZ et al., 2010), and quality of life (SUTBEYAZ et al., 2010). In individuals with PD, respiratory muscle weakness showed a statistically significant correlation with exercise capacity (HAAS et al., 2004). Therefore, respiratory muscle training can improve these important outcomes in this population.

Finally, studies investigating the combination of these training (inspiratory plus expiratory) in this population were not found. Performing combined inspiratory and expiratory muscle training using a single piece of equipment is cheaper and feasible, takes less time, and is easy to use. Thus, it is important to investigate the effects of t high-

intensity respiratory muscle training (combined inspiratory and expiratory muscle training) on inspiratory and expiratory muscle strength, inspiratory muscle endurance, peak cough flow, dyspnea, fatigue, exercise capacity, and quality of life in this population.

## **2.0.OBJECTIVES**

- Primary objective: To investigate the effects of high-intensity respiratory muscle training (combined inspiratory and expiratory muscle training) on inspiratory and expiratory muscle strength in individuals with PD.
- Secondary objective: To investigate the effects of high-intensity respiratory muscle training (combined inspiratory and expiratory muscle training) in improving inspiratory muscle endurance, peak cough flow, dyspnea, fatigue, exercise capacity, and quality of life in this population.

## **3.0.METHODS**

A prospective, superiority parallel-group randomized controlled trial, with concealed allocation, allocation ratio 1:1, blinded evaluations, and intention-to-treat analysis will be carried out at the Department of Physiotherapy, Universidade Federal de Minas Gerais (UFMG).

The project will be submitted to the Research Ethics Committee of the Universidade Federal de Minas Gerais. All consents for the development of the study were obtained. This trial will be registered at [www.ClinicalTrials.gov](http://www.ClinicalTrials.gov) and performed following the Consolidated Standards of Reporting Trials (CONSORT) (SCHULZ et al. 2010). All individuals will be instructed on the procedures and will sign a statement of informed consent. During the study, measures to prevent the spread of the coronavirus will be observed, such as attendance of only one participant per time, use of mask and alcohol gel (COMITÊ PERMANENTE DE ENFRENTAMENTO DO NOVO

CORONAVÍRUS DA UFMG, 2020; MINISTÉRIO DA SAÚDE, 2020).

### **3.1. Participants**

A non-probabilistic sample will be recruited from the community through contact with health centers, research groups, and university extension programs. Individuals will be included according to the following criteria: Parkinson's disease diagnosed by a neurologist; ability to walk independently, with or without assistive devices; taking antiparkinsonian medication, and who have been medically stable for at least six months; classified between stages 1-3 of the modified Hoehn & Yahr Scale (SCHENKMAN et al., 2001); maximum inspiratory pressure less or equal to -80 cmH2O or maximum expiratory pressure less or equal to 90 cmH2O. Individuals will be excluded according to the following criteria: possible cognitive impairment as determined by cutoff scores (in points) of the Mini-Mental Status Examination; use of deep brain stimulation (DBS); smokers or who stopped smoking less than six months ago; have been affected by respiratory or cardiac infections in the last month; had any other neurological, musculoskeletal, cardiovascular or respiratory disorders that could affect their ability to perform the tests.

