### **3.5. Instruments**

#### **3.5.1. Primary Outcomes**

##### **3.5.1.1. Inspiratory Muscle Strength**

Inspiratory muscle strength will be measured using MIP. Measurements will be performed using a digital manovacuometer (NEPEB-LabCare/UFMG, Brazil) and reported in cmH2O (PESSOA et al., 2014; PESSOA et al., 2015). The determination of the manovacuometer variables is performed using the MANOVAC 4.0 software. The manovacuometer is the gold standard instrument to measure respiratory muscle strength (PESSOA et al., 2014). Individuals will perform inspirations against an obstructed airway within the mouthpiece. The collection will be performed with the individual sitting in a chair, with the feet and back supported and the torso at a 90-degree angle with the hip. A conventional mouthpiece and nose clip will be used (PESSOA et al., 2015). Individuals will be instructed to breathe comfortably two to three times at tidal volume level. Five acceptable measurements will be taken. The highest pressure of three reproducible measurements, with less than 10% variability, will be recorded and used for analysis (PESSOA et al., 2015).

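### The inspiratory limb of the eligibility criterion, read as a signed inequality, selects strength instead of weakness, and the protocol states no sign convention for MIP

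*Protocol*

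**What the plan says.** The eligibility criterion in section 3.1 has two limbs, and either one is enough: "maximum inspiratory pressure less or equal to -80 cmH 2 O or maximum expiratory pressure less or equal to 90 cmH 2 O".

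The purpose of the intervention is given at the end of section 1.2: "when muscle weakness is observed, interventions to increase muscle strength of both muscle groups should be performed".

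MIP appears with two sign conventions:

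- **Positive magnitude, section 1.2.** PD men 65.0 (SD 17.9) and PD women 55.6 (SD 18.8) cmH2O, against healthy values of 86.9 and 70.0. The PD figures are described as "values significantly lower in individuals with PD", so a smaller number means a weaker patient.
- **Negative number, section 1.3.** Training gains are reported as "an increase in MIP was found, ranging from -1.28cmH 2 O" up to -16, and as "an improvement in MIP of -43cmH 2 O and MEP of 51cmH 2 O was found".
- **Negative number, section 3.1.** The cut-off itself: "maximum inspiratory pressure less or equal to -80" cmH2O.

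For the primary outcome, section 3.5.1.1 says: "The highest pressure of three reproducible measurements, with less than 10% variability, will be recorded and used for analysis". No sign is printed there, and section 3.5.1.2 uses nearly the same wording for MEP.

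**The concern.** The two limbs use the same comparison words on scales that run in opposite directions. For MEP, a value at or below a positive cut-off identifies weak expiratory muscles. For MIP with a minus sign, a value at or below the cut-off identifies an effort of 80 cmH2O or more, which is the stronger end. Nothing in the protocol argues for recruiting patients because their inspiratory muscles are strong.

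This is an operative threshold. A screener, monitor or programmed eligibility check that applies the printed inequality to signed values gets the wrong answer on that limb. An eligibility audit could not then say which inclusions were correct and which were deviations. MIP is one of the two primary outcomes, and only 34 participants are planned.

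**Working it through.** **Direction of the inequality.** The cut-off is not a calculated figure, so there is none to reproduce. The check is the ordering of signed numbers:

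- -100 <= -80 is true: the stronger patient meets the limb.
- -60 <= -80 is false: the weaker patient fails it.

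**Share meeting each limb.** Inputs are the PD means and SDs in section 1.2: MIP as listed above; MEP 81.9 (SD 14.7) for men and 64.4 (SD 21.9) for women. Normal distributions are assumed, and Phi is the standard normal distribution function.

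- MIP magnitude <= 80, men: Phi((80 - 65.0)/17.9) = Phi(0.838) = 0.799. The literal limb is met by 1 - 0.799 = 0.201.
- MIP magnitude <= 80, women: Phi((80 - 55.6)/18.8) = Phi(1.298) = 0.903. The literal limb is met by 0.097.
- MEP <= 90, men: Phi((90 - 81.9)/14.7) = Phi(0.551) = 0.709.
- MEP <= 90, women: Phi((90 - 64.4)/21.9) = Phi(1.169) = 0.879.

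**Effect of the OR.** Let a = P(MIP magnitude <= 80), e = P(MEP <= 90), and b = P(both), from a bivariate normal. The MIP-MEP correlation is not in the protocol, so I assume a range of 0 to 0.7.

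- Wrongly rejected by the literal reading (weak MIP, MEP above 90): a - b. As a share of inspiratory-weak patients: (a - b)/a.
- Wrongly admitted (MIP magnitude above 80 and MEP above 90): 1 - a - e + b.
- Eligible overall: 1 - a + b (literal) or a + e - b (magnitude).

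| | Correlation | Rejected, of all | Rejected, of inspiratory-weak | Admitted though weak on neither, of all | Eligible, literal | Eligible, magnitude |
|---|---|---|---|---|---|---|
| Men | 0 | 0.232 | 0.291 | 0.058 | 0.768 | 0.942 |
| Men | 0.7 | 0.149 | 0.187 | 0.141 | 0.851 | 0.859 |
| Women | 0 | 0.109 | 0.121 | 0.012 | 0.891 | 0.988 |
| Women | 0.7 | 0.070 | 0.077 | 0.052 | 0.930 | 0.948 |

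For example, for men at zero correlation b = 0.799 x 0.709 = 0.567, so a - b = 0.232 and 0.232/0.799 = 0.29.

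The two kinds of error trade off. As the correlation rises, fewer weak patients are lost and more strong ones are let in. For men at 0.7 the overall eligible share is almost the same under both readings (0.851 and 0.859), so the screening success rate would not reveal a misreading.

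**The outcome rule.** Take three illustrative efforts of 62, 60 and 58. As magnitudes, the highest is 62. If they were stored as negatives and the numeric maximum were taken, the result would be -58, a shift of (62 - 58)/62 = 6.5%. The 10% variability limit keeps any such shift under roughly 10%.

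**The case against.** The strongest reply is that the protocol shows how its minus sign works. Section 1.3 calls changes of -1.28 to -16 an increase, and sets -43 for MIP beside 51 for MEP as comparable improvements. There the sign marks inspiratory direction and size is judged by magnitude. On that usage the criterion means 80 or weaker, in line with the MEP limb and the rationale. Sections 3.3.1 and 3.5.2.1 also treat MIP as a magnitude when they set loads at 60% and 50% of it. This stands as evidence of intent, and it lowers the severity. It does not make the printed inequality correct, and no convention is stated that would make it so.

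A reader might infer two stronger points, which the protocol does not support:

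- **That inspiratory-weak patients are generally shut out.** They are not. With "or maximum expiratory pressure less or equal to 90" as a sufficient alternative, most of them qualify on MEP even under the literal reading. The 29% (men) and 12% (women) are upper bounds that assume zero correlation.
- **That the sign problem reverses the primary outcome.** Section 3.5.1.1 prints no minus sign, and its wording naturally means the strongest effort. Nothing in the protocol says signed values will be exported. Even if they were, any selection shift is bounded as shown above and follows the same rule in both arms and at all visits. Changing the sign of every MIP value leaves the F and p values of the repeated-measures ANOVA in section 3.7 unchanged. Only the sign of Cohen's d would change, and section 3.7 grades that by size.

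**Conclusion.** The point holds for the inspiratory limb of the eligibility criterion. As printed, that limb contradicts the MEP limb beside it, the rationale in section 1.2 and the positive MIP values in the same section. Under the literal reading about 20% of men and 10% of women meet it, instead of about 80% and 90%.

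The net effect on enrolment is smaller because of the OR: about 19-29% of inspiratory-weak men and 8-12% of inspiratory-weak women rejected, and about 6-14% of all men and 1-5% of all women admitted though weak on neither cut-off. These shares assume normality, an MIP-MEP correlation between 0 and 0.7, and that the PD sample in section 1.2 resembles the patients screened. They describe what would follow if staff applied the inequality literally. The protocol does not show that they will.

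Severity is moderate: a wording error in an operative criterion, with fairly evident intent. It is not an error in the primary outcome or its analysis.

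**What to change.** - State one sign convention for MIP, for example absolute value in cmH2O, and use it in sections 1.2, 1.3 and 3.1.
- Reword the inspiratory limb in section 3.1 so that it selects weakness in the same direction as the MEP limb and the rationale. Leave the number 80 as it is; this point takes no view on the cut-off value.
- As a clarification only, say in section 3.5.1.1 that the highest pressure is the one of largest magnitude.

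The cost is a few lines of text. No extra data are needed, and the sample size and analysis do not change. If screening has begun, the log should show which reading was used. Only patients with MEP above 90 need checking, because everyone else qualifies under both readings.
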